#### Classification loss

$$\begin{array}{c} \begin{array}{c} L_{\mathrm{cls}}=-\lambda_{\mathrm{cls}}\sum_{C\in \mathrm{types}}\sum_{c\in \mathrm{classes}\;}\\ \left[{\hat{p}}_{i}\left(c\right)\log\left(p_{i}\left(c\right)\right)+\left(1-{\hat{p}}_{i}\left(c\right)\right)\log\left(1-p_{i}\left(c\right)\right)\right] \end{array} \end{array}$$

Where, 
${\hat{p}}_{i}\left(c\right)$
 represents the prediction class,
$\;p_{i}\left(c\right)$
 represents the true class, C represents the types of classification (WHO, IDH, ATRX, or 1p19q), and c represents classes in each classification. 
$\lambda_{\mathrm{cls}}$
 represents the weight coefficient of classification loss.

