### Outcomes

#### Primary outcomes

The molecular type of 2021 WHO-CNS classification will be the primary outcome, including IDH (mutant/wild), ATRX (retain/lost), 1p/19q (codel/intact), CDKN2A/B (retain/lost), TERT/EGRF/+7/−10 (retain/lost), H3.3 G34 (mutant/wild), H3K27M mutant.

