### Model development preprocess

Each patient in the dataset had MR scans of four sequences: T1C, T1, T2, T2 flair, and tumor mask, along with classification labels.

The goal of this network is to segment three regions of glioma, including enhanced tumor area (ET), non-enhanced tumor area (NET), and edema area (ED); The tumor’s location, size, and classification information obtained from the target detection network were combined with the CTC numerical feature to differentiate the histological type and molecular type.

Four different experienced neurosurgeons, who also received guidance from a senior neuroradiologist (>10 years of clinical experience), applied Segmentation and Segment Editor modules to manually segment the original MRI dataset. All scans have been co-registered to the same anatomical reference using a rigid transform method on the 3D-slicer registration module. Skulls of the brain MRI were removed by 3D-slicer software that can eliminate the influence of skull areas with high-intensity signals. MR scans often display intensity non-uniformities due to variations in the magnetic field. Therefore, N4 bias field correction was used before the image input. We use data augmentation to increase the size of the dataset. To prevent over-fitting in training, data augmentation was used to expand the dataset.

The data augmentation methods used are as follows: (1) Adding random noise to the voxel, the noise worth ranged between −0.1 times and 0.1 times the standard deviation of the voxel. (2) Image size was changed to the original 0.9–0.1 times. (3) Random rotation and translation, with rotation ranging from −20 to +20°, and translation ranging from −30 to +30 and −15 to +15, respectively. (4) Random flip.

According to the 2021 WHO classification criteria, the molecular types of glioma were divided into 11 subcategories, and the histological type was divided into three grades. The grades, segmentations, and subcategories labels of each patient were one-hot encoded. In the preprocessing step, anchor boxes of the tumors were automatically generated according to the segmentation labels. The anchor box was the ground truth of the target detection task.

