### Classification part

The features from the target detection network contained 14 classification features (WHO 3, molecular type 11) and 6 box features (location 3, size 3). The location and size of the prediction box represented the location and size of the glioma to some extent. These numerical features were combined with CTC numerical features and then input into the MLP module which is shown in Figure 5. The outputs of MLP were input into the softmax layer to obtain the final classification of WHO grades and molecular subtypes.

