### Loss function

The loss function consists of four parts: coordinate loss, confidence loss, classification loss, and segmentation loss. The confidence loss and regression loss in the object detection part refer to the YOLOv4 model (Bochkovskiy et al., 2020). Cross entropy loss was used as classification loss and segmentation loss.

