To date, with the in-depth study of LB, CTC as an important branch has been applied to the non-invasive diagnosis of glioma. In our previous study (Qi et al., 2021), it has been confirmed that peripheral blood CTC is related to IDH mutant. However, the relationship between CTC and other important molecular targets has not been further explored, and we have not found other similar studies. In this study, we combine CTC count as a very important parameter with the DL model to explore its value in molecular and graded noninvasive diagnosis of glioma, which is unprecedented in the current study. However, it must be clarified that some glioma subtypes are assigned to fewer training samples and cannot rely on the model for subtype diagnosis. Therefore, we further proposed CTC sequencing of individual molecular targets as the basis for the diagnosis of glioma subtypes. Since the inherent black-box nature of deep learning models and less transparency, we will add relative modules to improve the understandability of existing models based on the premise of the stable prediction performance of the models in the future (Dasanayaka et al., 2022).

Since the publication of the WHO-CNS classification guidelines in 2021, scholars around the world have been committed to the application of radiomics or LB techniques to achieve “precisely integrated prediction” of gliomas before surgery, since the noninvasive prediction of important molecular markers is essential to guide the treatment of patients who are inoperable or have tissue biopsy. Simply relying on radiomics features to find the correlation with the molecular pathological features of gliomas can no longer meet the need for an accurate diagnosis of gliomas. CTC features are a promising biomarker that may provide new directions in the exploration of “precision diagnosis” based on the radiomics. How to combine the preoperative radiomics features, CTC features or other LB markers of glioma patients is the direction that requires the joint efforts of global scholars in the future, At the same time, it is necessary to provide matched molecular marker information of glioma patients to ensure the feasibility of the study.

We firmly believe that this innovative work will surely lay a good foundation for the “precisely integrated prediction” of glioma and shed a new direction for future research.

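### Four of the seven primary molecular items have no term in the stated training loss, and the 11 molecular classes are neither listed nor consistent with that loss

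*Protocol article*

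**What the plan says.** Five parts of the protocol article bear on what the model is trained to predict.

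- **Primary outcomes.** The primary outcome is molecular type, "including IDH (mutant/wild), ATRX (retain/lost), 1p/19q (codel/intact), CDKN2A/B (retain/lost), TERT/EGRF/+7/−10 (retain/lost), H3.3 G34 (mutant/wild), H3K27M mutant". That is seven items, and none is exempted. The abstract's Methods and the objectives at the end of Related study say that the deep learning model is to diagnose, and be evaluated on, all molecular subtypes.
- **Loss function.** "The loss function consists of four parts: coordinate loss, confidence loss, classification loss, and segmentation loss". The Classification loss section then defines its outer sum: "C represents the types of classification (WHO, IDH, ATRX, or 1p19q), and c represents classes in each classification".
- **Model development preprocess and Classification part.** "the molecular types of glioma were divided into 11 subcategories, and the histological type was divided into three grades". On coding, "The grades, segmentations, and subcategories labels of each patient were one-hot encoded". The detection network passes on 14 classification features, 3 for WHO grade and 11 for molecular type. At the end, "The outputs of MLP were input into the softmax layer to obtain the final classification of WHO grades and molecular subtypes".
- **Learning curve section.** It refers to three classification loss curves.
- **Discussion.** It concedes that "some glioma subtypes are assigned to fewer training samples and cannot rely on the model for subtype diagnosis", and proposes CTC sequencing of individual targets for subtype diagnosis.

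**The concern.** A supervised network learns to predict a label only if that label enters its loss. If the loss covers fewer markers than the primary outcome, a team building from this document has no trained prediction for the remaining markers and nothing to report for them on accuracy, precision or recall. If the 11 output classes are also undefined, two teams could build different models from the same text and report different primary endpoints. The set of primary markers could then be settled after performance has been seen. For a primary outcome described as the full molecular type, this affects what the study may conclude.

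**Working it through.** The check is a count and a comparison of sections. It does not use the sample size.

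**1. The plan's own figure.** WHO 3 + molecular 11 = 14 classification features. This agrees with the 14 in Classification part, and the 11 agrees with Model development preprocess.

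**2. Which loss components can carry a marker label.** Coordinate loss uses box positions, confidence loss uses box overlap, and segmentation loss uses voxel labels. Only the classification loss can use marker labels, and the total loss is the plain sum of the four.

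**3. Primary items against the types in the classification loss.**

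| Primary item | Named in the loss |
|---|---|
| IDH | yes |
| ATRX | yes |
| 1p/19q | yes |
| CDKN2A/B | no |
| TERT/EGFR/+7/−10 | no |
| H3.3 G34 | no |
| H3K27M | no |

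Named: 3. Not named: 7 − 3 = 4. With WHO grade the loss has 3 + 1 = 4 types. Covering grade and every primary item would take 7 + 1 = 8.

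**4. The 11 classes against the loss.** Three molecular markers give 3 units at one per marker, 3 × 2 = 6 at one per level, or 2³ = 8 joint combinations. None is 11.

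**5. The 11 classes against the primary outcome.**

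- One unit per item: 7.
- Levels as listed, with H3K27M having one: 6 × 2 + 1 = 13.
- Two levels for every item: 7 × 2 = 14.
- Each named alteration counted separately (IDH, ATRX, 1p/19q, CDKN2A, CDKN2B, TERT, EGFR, +7, −10, H3.3 G34, H3K27M): 11.

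The last count matches. It describes a vector in which several entries can be positive at once, which sits badly with one-hot labels and a softmax. Eleven mutually exclusive tumour subtypes would suit one-hot coding and a softmax, but would not be the marker-by-marker outcome that Primary outcomes lists. The text does not say which is meant, so a mismatch with the primary outcome is not shown. Either reading still conflicts with the three molecular types in the loss.

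**6. Number of classification losses.** The Learning curve section has three curves and the Classification loss section has four types. The figure is not available here, so the reason for the difference cannot be checked.

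**7. Which markers rest on the model.** The abstract and objectives say all of them. The Discussion says not all, without naming the exceptions. Primary outcomes makes no distinction.

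**The case against.** The strongest reply is that the bracket defining C is shorthand. The objectives name the same three markers and then leave the list open, and 11 molecular features are more than three markers need, so the authors may have trained on more than the bracket shows. That is plausible. It is also an inference from the sections disagreeing: the bracket carries no sign of being open, and no other text gives the remaining markers a training term. The reply lowers confidence about what was built but leaves the inconsistency in place.

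Four stronger readings are tempting and are not supported.

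- A reader might infer that the study cannot deliver its primary outcome. The loss list may be incomplete, Data collection includes CTC sequencing results, and the Discussion offers that sequencing as a route to subtype diagnosis outside the network. Primary outcomes does not require the imaging model alone to determine molecular type.
- A reader might infer that seven two-level markers require 13 or 14 outputs, so that 11 must be wrong. A binary marker needs only one output, and one count of the named alterations gives exactly 11.
- A reader might infer that the softmax prevents co-occurring alterations, such as an IDH mutation with ATRX loss, from both being called. That follows only if the 11 classes are individual markers under one shared softmax. The loss sums over types and then over classes within each type, which points towards separate coding per marker, and a combined subtype could hold both alterations in one class. The architecture is not settled by the text.
- A reader might add that rare markers will have imprecise recall. The document gives no marker prevalence, and the point would be the same if the loss listed all seven items.

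A journal article may leave architectural detail to a fuller document. That excuses an omission, but not two stated lists of targets that differ.

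**Conclusion.** The point holds as an inconsistency in the stated specification, and it should be corrected before final training. As written, four of the seven primary items have no term in the training loss. The 11 molecular classes are undefined in the text and do not fit the three molecular types in the loss. Their fit to the primary outcome cannot be determined. The document also disagrees with itself on the number of classification losses (three or four) and on whether the model covers all subtypes.

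The count of four assumes that the bracket in Classification loss is complete and that the TERT/EGFR/+7/−10 entry is one item, as Primary outcomes lists it. If the bracket is abbreviated, the defect is an incomplete definition of the primary model rather than untrained markers, and the same correction is needed. The figures that might list the 11 classes are not available here; any such list would still have to be reconciled with the loss.

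**What to change.** 1. List the 11 molecular classes and map each to the seven primary items, saying whether they are single alterations, marker levels or mutually exclusive subtypes.
2. Make the classification loss name every primary marker that the model is to predict. Give each marker its own output head, either a sigmoid or a two-class softmax, so that co-occurring alterations can both be called. With all seven items and three grades this is 3 + 7 = 10 output units with sigmoids, or 3 + 7 × 2 = 17 with two-class heads.
3. State before final training which primary markers are assessed by the model and which by CTC sequencing, and limit the model's primary claim to the former. Bring the abstract, objectives, Primary outcomes and Discussion into line.
4. Reconcile the number of classification loss curves with the number of types in the loss.

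The cost is a small change to the output layer and loss, retraining of any part already trained on a different target set, and edits to the outcome wording. The downside is a possibly narrower primary claim. A minimum number of positives per marker, or descriptive status for rare markers, would be a design choice and is not needed to resolve this point.

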#### Segmentation loss

$$\begin{array}{c} L_{seg}=-\lambda_{seg}\sum_{c=1}^{C_{seg}}\log\frac{\exp\left(x\right)}{\sum_{C_{seg}}^{i=1}\exp\left(x\right)}y \end{array}$$

x
is the output of the segmentation head, 
y
 is the one-hot code of the segmentation label, 
$C_{seg}$
 represents the number of classes that need to be segmented, and 
$\lambda_{seg}$
 represents the segmentation loss.

The total loss function is the sum of the four loss functions, as shown in equation

$$\begin{array}{c} L_{\mathrm{object}}=L_{\mathrm{coord}}+L_{\mathrm{conf}}+L_{\mathrm{cls}}+L_{\mathrm{seg}} \end{array}$$

### Evaluation index

#### Classification index

The classification indexes used in this paper include accuracy, precision, and recall, which will be introduced one by one in the following, and the confusion matrix is used to calculate the classification metrics (Stehman, 1997).

**Accuracy:** The accuracy represents the proportion of correctly predicted samples in the total sample, as shown in the equation:

$$\begin{array}{c} Accuracy=\frac{TP+TN}{TP+FN+FP+TN} \end{array}$$

**Precision:** Precision represents the proportion of truly positive samples among the samples predicted to be positive by the model, as shown in the equation:

$$\begin{array}{c} Precision=\frac{TP}{TP+FP} \end{array}$$

**Recall:** For all positive samples, Recall represents the proportion of actual positive samples that are predicted to be positive, as shown in the equation:

$$\begin{array}{c} Recall=\frac{TP}{TP+FN} \end{array}$$

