**Methods:**

This is a double-center, ambispective, diagnostical observational study. One public database named the 2019 Brain Tumor Segmentation challenge dataset (BraTS) and two original datasets, including the Second Affiliated Hospital of Nanchang University, and Renmin Hospital of Wuhan University, will be used to develop the multi-task DL radiomic model. As one of the LB techniques, circulating tumor cell (CTC) parameters will be additionally applied in the DL radiomic model for assisting the “integrated diagnosis” of glioma. The segmentation model will be evaluated with the Dice index, and the performance of the DL model for WHO grading and all molecular subtype will be evaluated with the indicators of accuracy, precision, and recall.

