### Sample size

A sample of 400 achieves 90% power to detect a difference of 0.1000 between the area under the ROC curve (AUC) under the null hypothesis of 0.7000 and an AUC under the alternative hypothesis of 0.8000 using a two-sided z-test at a significance level of 0.05000. The data are discrete (rating scale) responses. The AUC is computed between false positive rates of 0.000 and 1.000. The ratio of the standard deviation of the responses in the negative group to the standard deviation of the responses in the positive group is 1.000.

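### The 400 patients are justified by power for an AUC test, but the stated evaluation is accuracy, precision and recall, and no AUC analysis or target label is specified

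*Protocol article*

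**What the plan says.** The Sample size section of the protocol article rests on a single hypothesis test: "A sample of 400 achieves 90% power to detect a difference of 0.1000". The quantity compared is an AUC, 0.80 against a null of 0.70, by a z-test at the two-sided 5% level. The section adds that "The data are discrete (rating scale) responses", that the AUC covers false positive rates from 0 to 1, and that the ratio of standard deviations is 1. It does not give the share of positive patients.

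The evaluation is stated twice. In the abstract, under Methods, "the performance of the DL model for WHO grading and all molecular subtype will be evaluated with the indicators of accuracy, precision, and recall". In the body, under Classification index, "The classification indexes used in this paper include accuracy, precision, and recall"; these are computed from a confusion matrix and each has a formula. The next two sections add IOU for detection and Dice for segmentation.

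Primary outcomes lists seven marker items (IDH, ATRX, 1p/19q, CDKN2A/B, a combined TERT/EGFR/+7/−10 item, H3.3 G34 and H3K27M). None is singled out for the powered test.

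**The concern.** A sample-size statement is useful only if it refers to an analysis that will be done. Here the powered analysis is a test on one AUC, while the evaluation sections describe three indices taken from a confusion matrix. A confusion matrix describes one operating point. It does not give an area over the full range of false positive rates.

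Two things are at stake. First, the only power claim in the article is not attached to any result that the article says it will report. Second, the indices that are listed have no null value, target or margin, so nothing shows whether 400 patients are enough for them. With seven marker items and no primary one, it is also open which AUC would be held against 0.70.

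**Working it through.** **1. Where AUC appears.** Outside Sample size, an area under the ROC curve occurs only in Related study, as another group's result. It is absent from the abstract's Methods, from Primary and Secondary outcomes, and from the classification, detection and segmentation indices. No section describes a ROC analysis or a comparison with 0.70.

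**2. Can the 400 be reproduced?** Inputs from Sample size: AUC 0.70 against 0.80, two-sided alpha 0.05 (z = 1.960), power 90% (z = 1.282). The share of positives p is not given, so it is varied. With R = (1 − p)/p:

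n_pos = [(1.960·√V(0.70) + 1.282·√V(0.80)) / 0.10]², and N = n_pos / p.

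Three variances were tried:
- Rating data: V(A) = 0.0099·exp(−a²/2)·[(5a² + 8) + (a² + 8)/R], a = 1.414·z(A).
- Binormal, SD ratio 1: V(A) = f²(1 + 1/R + a²/2) + g²(1 + R)/(2R) + f·g·a, with a = √2·z(A), E = exp(−a²/4), f = E/√(4π), g = −aE/√(16π).
- Hanley-McNeil: Var(A) = [A(1−A) + (n₁−1)(q₁−A²) + (n₀−1)(q₂−A²)]/(n₁n₀), q₁ = A/(2−A), q₂ = 2A²/(1+A), where n₁ and n₀ are the numbers of positives and negatives. N is the smallest total that reaches 90% power.

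Worked example, rating data, p = 0.25 (R = 3): V(0.70) = 0.1023 and V(0.80) = 0.0889. So n_pos = [(1.960·0.3198 + 1.282·0.2981)/0.10]² = 10.088² = 101.8, and N = 101.8/0.25 = 407.

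| Share positive (assumed) | N, rating data | N, Hanley-McNeil | N, binormal |
|---|---|---|---|
| 50% | 283 | 253 | 239 |
| 30% | 358 | 342 | 285 |
| 25% | 407 | 394 | 319 |
| 20% | 484 | 475 | 374 |
| 10% | 885 | 890 | 665 |

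At 25% positives, power with 400 patients is 89.5% (rating data) or 90.5% (Hanley-McNeil). Under the binormal variance, 400 matches 90% between 15% (N = 469) and 20% (N = 374). The 400 is therefore a plausible AUC calculation, but it cannot be confirmed without the share of positives. At 10% positives, power with 400 is 57%, 56% and 68% in the order of the columns.

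**3. Does the AUC difference carry over to a listed index?** Take an equal-variance binormal model, d = √2·z(AUC), so d = 0.742 at AUC 0.70 and 1.190 at AUC 0.80. Accuracy at cut-off t is p·[1 − Φ(t − d)] + (1 − p)·Φ(t), which is largest at t = d/2 + ln[(1 − p)/p]/d. At p = 0.50 this reduces to Φ(d/2), which gives Φ(0.371) = 0.645 and Φ(0.595) = 0.724.

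| Share positive (assumed) | Best accuracy, AUC 0.70 | Best accuracy, AUC 0.80 | Gain |
|---|---|---|---|
| 50% | 0.645 | 0.724 | 0.079 |
| 30% | 0.720 | 0.769 | 0.049 |
| 10% | 0.900 | 0.904 | 0.004 |

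The same AUC difference can be a clear or a negligible gain in accuracy, depending on how common the marker is. Power of 90% for the AUC test therefore implies no fixed power for accuracy. The article gives no null or target from which power for precision or recall could be worked out either.

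**The case against.** **The list of indices may not be exhaustive.** The verb used is *include*, the softmax outputs described under Classification part would allow an AUC to be computed, and a condensed article may leave ROC details to a fuller plan. This stands to the extent that one cannot say the AUC test will never be run, only that it is not specified. It does not remove the mismatch: the article does not merely omit its metrics, it states them twice, and neither list matches the analysis that it powers.

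**The plan does have a null.** For AUC it does (0.70), and that is fully stated. The gap concerns only the three listed indices.

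**Stronger readings.** A reader might infer that a useless model could pass as excellent, because calling every patient negative gives an accuracy of 1 − prevalence. The plan does not support that. Such a model has recall 0 and undefined precision, both planned indices would expose it, and the article gives no marker frequencies. A reader might also object that specificity is missing, but it follows from the confusion matrix. Nor do the documents show that 400 is miscalculated. Finally, the Discussion already concedes that some subtypes have too few training samples for the model to be relied on and proposes CTC sequencing for them, so rare markers are not left to accuracy alone.

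**Conclusion.** The point holds as an internal inconsistency. The stated 90% power and 5% error rate belong to an AUC test that the article attaches to no outcome, index or label, and they do not transfer to accuracy, precision or recall. The conclusion rests on the article's own text. Only the sizes depend on assumptions.

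Those assumptions are the share of positives (varied, since it is not stated) and, for the accuracy comparison, the equal-variance binormal model. On them, the AUC contrast corresponds to an accuracy gain of anywhere from 0.004 to 0.079 between 10% and 50% positives. For the AUC test itself, 400 gives about 90% power near 25% positives under the rating-data or Hanley-McNeil variance, whereas 665 to 890 patients would be needed at 10%. The power would also be lower if the 400 includes patients used for training, which Sample size does not say.

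**What to change.** In the abstract's Methods and in Classification index:
- Name AUC, with a 95% CI and the test against 0.70, as the primary evaluation index for one named molecular label, in patients not used for training.
- Report AUC with CIs for the other markers as secondary, without claiming 90% power. Testing all of them against 0.70 would not inherit the stated power and would raise multiplicity across the seven marker items.
- Keep accuracy, precision and recall as descriptive measures, shown beside marker prevalence.

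In Sample size, name the label, the assumed share of positives and the number of evaluation patients behind the 400. Restate the power if these differ from what 90% requires.

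Alternatively, keep the three indices as the main evaluation and rewrite the sample-size justification for them, with a null or target value.

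The cost is small: a little more analysis work, and no new data for the AUC itself because the model already outputs class probabilities. The drawback is that the restated power may be less favourable than 90%, particularly if the chosen label is uncommon or training patients are counted in the 400.
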